# Impact of remote ischemic preconditioning preceding coronary artery bypass grafting on inducing neuroprotection (RIPCAGE): study protocol for a randomized controlled trial

**DOI:** 10.1186/1745-6215-15-414

**Published:** 2014-10-27

**Keywords:** coronary artery bypass grafting, functional, magnetic resonance imaging, neurocognitive outcome, remote ischemic preconditioning

## Abstract

**Background:**

Neurological complications after cardiac surgery have a profound impact on postoperative survival and quality of life. The increasing importance of strategies designed to improve neurological outcomes mirrors the growing risk burden of the contemporary cardiac surgical population. Remote ischemic preconditioning (RIPC) reduces adverse sequelae of ischemia in vulnerable organs by subjecting tissues with high ischemic tolerance to brief periods of hypoperfusion. This trial will evaluate the neuroprotective effect of RIPC in the cardiac surgical arena, by employing magnetic resonance imaging (MRI) and neurocognitive testing.

**Methods:**

Patients scheduled for elective coronary artery bypass grafting with the use of cardiopulmonary bypass will be screened for the study. Eligible patients will be randomized to undergo either a validated RIPC protocol or a sham procedure. The RIPC will be induced by inflation of a blood pressure cuff to 200 mmHg for 5 minutes, followed by a 5-minute reperfusion period. Three sequences of interchanging cuff inflations and deflations will be employed. Neurocognitive testing and MRI imaging will be performed preoperatively and on postoperative day 7. Paired pre- and postoperative neurocognitive and neuroimaging data will then be compared. The primary composite outcome measure will consist of new ischemic lesions on brain MRI, postprocedural impairment in brain connectivity on resting-state functional MRI (rs-fMRI), and significant new declines in neurocognitive performance. The secondary endpoint measures will be the individual components of the primary endpoint measures, expressed as continuous variables, troponin T release on postoperative day 1 and the incidence of major adverse cardiovascular events at 3 months postoperatively. Major adverse cardiovascular events, including accumulating cardiovascular mortality, stroke, nonfatal myocardial infarction, and rehospitalization for ischemia, will form a composite endpoint measure.

**Discussion:**

This trial will aim to assess whether RIPC in patients subjected to surgical myocardial revascularization employing cardiopulmonary bypass initiates a neuroprotective response. Should the results of this trial indicate that RIPC is effective in reducing the incidence of adverse neurological events in patients undergoing coronary artery bypass grafting, it could impact on the current standard of care.

**Trial registration:**

ClinicalTrials.gov NCT02177981.

## Background

Neurological impairment following coronary artery bypass grafting may take on the form of stroke or postoperative cognitive dysfunction. The former is rare, but potentially devastating. However, a decline in attention, memory, or fine motor skills can frequently be documented by sensitive neurocognitive testing [1]. Postoperative deterioration in neurocognitive capacity is often discrete, but exerts an adverse impact on the quality of life. Its reversibility is subject to interpatient variability, with 25% of patients still exhibiting signs of cognitive impairment 6 months after surgery [1, 2].

Ischemic preconditioning exploits the endogenous protective potential against sustained ischemia incurred by brief episodes of ischemia and reperfusion [3]. The phenomenon is probably triggered by both neuronal and humoral pathways [3]. In an experimental setting, transfer of coronary effluent from an ischemically preconditioned rabbit to an ischemic-preconditioning-naïve animal reduced myocardial infarct size in the latter [4]. This observation consolidated the hypothesis of a humoral protective mediator [4]. This hypothesis was corroborated by the induction of protection in a denervated donor heart by limb ischemia [5]. The fact that ischemic-preconditioning-induced organ protection was inhibited by a ganglion blocker, however, gave credence to the idea of the existence of underlying neural pathways [3].

Remote ischemic preconditioning (RIPC) denotes the concept by which brief episodes of sublethal ischemia in tissues with high ischemic tolerance stimulate protection in distant organs from a subsequent severe insult [6]. It is conceptually much simpler to induce than conventional ischemic preconditioning, thereby expanding its clinical applicability. Several reports have demonstrated that RIPC protocols lead to reductions in myocardial injury following cardiac surgery [7, 8]. Thielmann *et al.*
[9] recently showed that RIPC induced by upper limb ischemia in patients undergoing elective coronary artery bypass grafting led to a reduction in troponin T release, which mirrored an observed reduction in mortality (ratio, 0.27; 95% confidence interval, 0.08 to 0.98; *P* = 0.046).

The relative paucity of effective management options to treat neurological dysfunctions once they have become clinically manifest provides a strong impetus for defining strategies that reduce their incidence [10]. Ischemic preconditioning has been shown to induce ischemic tolerance in the brain via key survival signaling pathways, which promote synaptic and mitochondrial adaptations [11]. These modifications reduce the adverse impact of excitotoxicity, which is pivotal to ischemic neuronal injury [11]. Ischemic preconditioning produces two windows of protection. The early window of protection follows rapidly after the event that induced it [10], while delayed preconditioning occurs after a 24-hour delay [10]. The latter is protein synthesis-dependent, with subsequent protection extending for up to 96 hours. The benefits of early preconditioning are that it can be relied upon to promote organ protection immediately prior to an index event carrying a risk of brain injury [10]. In an experimental model, RIPC has been found to exert a beneficial effect on multiple variables acting as surrogate markers of brain injury following prolonged circulatory arrest [12]. These included a reduction in brain lactate release, a faster recovery of electroencephalographic activity and superior quantitative behavioral scores [12].

Magnetic resonance imaging (MRI) allows for sensitive delineation of the anatomical substrate underlying ischemic injury [13]. Its potential to detect clinically silent brain injury has been clearly recognized [14]. Specifically, hyperintensity on diffusion-weighted imaging, together with a decrease in the apparent diffusion coefficient, is effective in demarcating the core of acute ischemic lesions [13]. Combinations of different MRI signals provide complementary information on the evolution of organic neuropathology [13]. Resting-state functional MRI (rs-fMRI) is a novel instrument that focuses on functional brain connectivity, rather than attempting to define structural pathology [15]; it harbors the potential to identify the presence of anatomically divergent regions that operate in synchrony as large-scale neural networks [16]. These anatomically distributed regions act in concert to determine a variety of complex behavioral patterns.

In our study, coronary surgery using cardiopulmonary bypass will be considered the index deleterious event. The mechanisms of neurologic injury following cardiopulmonary bypass include ischemia, inflammation, cerebral edema, and hyperthermia [1]. Brain ischemia occurring during cardiac surgery might be the consequence of embolic showers consistently shown on transcranial Doppler during episodes of aortic manipulation, or procedure-associated hypoperfusion [1, 14].

Strategies designed to protect end-organ function are paramount in current cardiac surgical practice. The convergence of the ever-increasing patient-risk profile with the growing complexity of modern cardiac surgical procedures underscores the importance of defining algorithms that will maintain acceptable clinical outcomes.

We hypothesized that the neuroprotective potential of RIPC could translate into an improvement in neurological imaging or functional outcomes among cardiac surgical patients.

## Methods

### Study population

The study is designed as a single-center, prospective, randomized, double-blind controlled trial (Figure 1). Adult patients with multivessel coronary disease undergoing primary, elective coronary artery bypass grafting at the University Hospital Center Zagreb will be eligible for study enrollment. Following the process of primary triage, they will be approached by a study nurse who will provide detailed information about the trial. Written informed consent will be obtained from all patients prior to enrollment. Preoperative and postoperative exclusion criteria are summarized in Table 1.

**Figure 1 Fig1:**
[figure not shown]
**Flowchart depicting the screening, recruitment and randomization algorithm.** AMI, acute myocardial infarction; CABG, coronary artery bypass grafting; LVEF, left ventricular ejection fraction; MACCE, major adverse cardiac and cerebrovascular event; MRI, magnetic resonance imaging; NCT, neurocognitive testing, PVD, peripheral vascular disease; TIA, transitory ischemic attack.

**Table 1 Tab1:** **Study inclusion and exclusion criteria**

*Inclusion criteria*	*Rationale for inclusion*
Adult patients (18 to 80 years) undergoing primary coronary artery bypass grafting with the use of cardiopulmonary bypass	Population of interest
***Preoperative exclusion criteria***	***Rationale for exclusion***
Emergent coronary artery bypass grafting	Higher-risk profile
Recent acute myocardial infarction	Concurrent indication for dual antiplatelet therapy
History of stroke or transitory ischemic attack	Prior neurological condition
Structural brain abnormalities	Prior neurological condition
Carotid artery disease	Ineligible for study enrollment
Valve surgery	Ineligible for study enrollment
Left ventricular ejection fraction <30%	Higher-risk profile
Atrial fibrillation	Higher-risk of neurological complications
Renal failure	Higher-risk profile
Repeat coronary artery bypass grafting	Higher-risk profile
Off-pump coronary artery bypass grafting	Avoidance of cardiopulmonary bypass
Inability to provide consent	Ineligible for study enrollment
Contraindications for MRI	Ineligible for study enrollment
Peripheral vascular disease of upper extremities	Contraindication for remote ischemic preconditioning
***Postoperative exclusion criteria***	***Rationale for exclusion***
New-onset contraindication for MRI	Protocol violation
Hemodynamic instability	Inability to complete follow-up MRI

MRI, magnetic resonance imaging.

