### Allocation procedure

Randomization will be based on computer generated coding. Codes will be kept in sealed envelopes. These will be opened in the operating room by an anesthesiologist not involved in subsequent data accumulation or analysis. Patients randomized to the intervention arm will be subjected to brief periods of upper limb ischemia designed to induce RIPC, as described later. Patients assigned to the control arm will receive no ischemic preconditioning. Surgeons and intensive care physicians will be unaware of treatment allocation.

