### Intervention and control protocols

Remote ischemic preconditioning will be induced by alternating periods of upper limb ischemia and reperfusion. Transient arm ischemia will be produced by inflating a blood pressure cuff to 200 mmHg for 5 min, and then deflating it for 5 min. This sequence will be repeated three times after the induction of anesthesia and prior to the surgical incision. Our intervention protocol has been used previously and constitutes a validated protocol with beneficial effects exerted at the myocardial level [9]. Patients in the control group will also have a blood pressure cuff placed, but it will not undergo the aforementioned inflation-and-deflation cycles.

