### Outcome definitions

The primary composite outcome will consist of new ischemic lesions on brain MRI, impairment in brain connectivity on resting-state functional MRI (rs-fMRI) and postoperative cognitive dysfunction. Postoperative cognitive dysfunction will be defined as a decrease of at least one standard deviation in at least two components of neurocognitive testing.

The secondary endpoint measures will be:Volumetric quantification of areas of new ischemic lesions on structural brain MRI.Changes between pre- and post-rs-fMRI, expressed as continuous variables and compared among the intervention and control arms.Percentage declines in individual neurocognitive tests.Troponin T release on postoperative day 1.Incidence of major adverse cardiovascular events at 3 months postoperatively.

Major adverse cardiovascular events will comprise a composite endpoint measure, consisting of cardiovascular mortality, stroke, nonfatal myocardial infarction, and rehospitalization for ischemia. Perioperative myocardial infarction will be adjudicated in accordance to the definition supplied by the Joint European Society of Cardiology/American College of Cardiology Foundation/American Heart Association/World Heart Federation Task Force for the Redefinition of Myocardial Infarction [31]. Briefly, a troponin T value ten times the 99th percentile of the upper reference limit, coupled with electrocardiogram changes, new-onset coronary artery (or graft) occlusion, or imaging evidence of new wall motion abnormalities will meet the criteria for perioperative myocardial infarction [31]. Stroke will be a defined on the basis of either a new focal deficit lasting >24 hours or an imaging study suggestive of a new lesion in patients with prompt neurological recovery [32].

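### Table 1 excludes randomised patients from the study for events after surgery (haemodynamic instability, a new MRI contraindication), which may bias the comparison and reaches endpoints that need no MRI

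*Protocol article*

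**What the plan says.** Table 1 of the protocol article sets out the inclusion and exclusion criteria and has a separate block of postoperative exclusions with two entries:

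- "New-onset contraindication for MRI", with the rationale that it is a protocol violation;
- haemodynamic instability, with the rationale "Inability to complete follow-up MRI".

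The Study population section treats them as criteria of the same kind as the preoperative ones: "Preoperative and postoperative exclusion criteria are summarized in Table 1".

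On timing, the Allocation procedure section says of the sealed envelopes: "These will be opened in the operating room by an anesthesiologist not involved in subsequent data accumulation or analysis". The Intervention and control protocols section says of the cuff cycles: "This sequence will be repeated three times after the induction of anesthesia and prior to the surgical incision".

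The Outcome definitions section builds the primary composite from new ischaemic MRI lesions, impaired connectivity on rs-fMRI and postoperative cognitive dysfunction. Secondary endpoints include day-1 troponin T, percentage declines in the neurocognitive tests, and "Incidence of major adverse cardiovascular events at 3 months postoperatively". The Statistical analysis section does not say that patients who meet a postoperative exclusion criterion stay in any analysis.

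**The concern.** Preoperative exclusions define who is randomised. Postoperative exclusions remove people who already have been, on the basis of something that happened after treatment. If treatment changes the chance of that event, and the event goes with the outcome, the patients left in the two arms no longer differ only by allocation.

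The article supplies both links for instability. Its Background says "RIPC protocols lead to reductions in myocardial injury following cardiac surgery", and instability after surgery is a plausible consequence of myocardial injury. It also lists "procedure-associated hypoperfusion" among the possible causes of brain ischaemia during cardiac surgery.

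The rule also reaches further than its rationale. An impossible scan explains a missing MRI result. It does not explain removing the patient from the study, where troponin T, MACE and cognition can be recorded without a scanner. MACE includes cardiovascular death and stroke, so an unstable patient who later dies could be absent from the endpoint meant to count that death.

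**Working it through.** **1. The plan's own figure.** The Sample size section gives 70 patients from an exact sign test with effect size 0.20, α 0.05 and power 0.90, including an unquantified allowance for MRI contraindications and consent withdrawals. Reading the effect as 0.70 against 0.50, two-sided, the smallest N reaching 0.90 power is 65 (critical value 41, exact α 0.0464, power 0.910). N = 70 gives power 0.922 (exact α 0.0414). One could infer an allowance of 5/70 = 7.1%. But 70 is also the smallest N from which power stays at or above 0.90, and a one-sided test would need 53, implying 17/70 = 24%. So no planned exclusion rate can be recovered, and the allowance does not name instability.

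**2. Order of events.** Envelope opened in the operating room → RIPC or sham before incision → surgery → instability or new MRI contraindication → day-7 MRI. Both criteria fall after allocation and treatment.

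**3. Reach of the rationale.**

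| Endpoint | Needs the day-7 MRI? |
|---|---|
| New ischaemic lesions; lesion volume | Yes |
| rs-fMRI connectivity | Yes |
| Cognitive dysfunction; test declines | No |
| Troponin T, day 1 | No |
| MACE, 3 months | No |

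One of the three primary components and three of the five secondary endpoints do not depend on the scan.

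**4. What differential exclusion could do (all inputs assumed).** Let p be the true composite risk in an arm, e the share excluded and q the risk among those excluded. The risk among those retained is (p − e·q)/(1 − e).

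No true effect, p = 0.50 in both arms, 15% of controls and 5% of RIPC excluded, q = 1:

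- control (0.50 − 0.15)/0.85 = 0.412
- RIPC (0.50 − 0.05)/0.95 = 0.474
- RIPC minus control = +0.062

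Other cases, RIPC minus control:

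| Excluded, control / RIPC | q | True 0.00 | True −0.20 (0.50 vs 0.30) |
|---|---|---|---|
| 10% / 10% | any of 0.5, 0.8, 1.0 | 0.000 | −0.222 |
| 10% / 5% | 0.8 | +0.018 | −0.193 |
| 10% / 5% | 1.0 | +0.029 | −0.181 |
| 15% / 5% | 0.5 | 0.000 | −0.211 |
| 15% / 5% | 0.8 | +0.037 | −0.173 |
| 15% / 5% | 1.0 | +0.062 | −0.149 |
| 20% / 10% | 1.0 | +0.069 | −0.153 |

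Under no effect, swapping the arms reverses the sign: 5% of controls and 15% of RIPC with q = 1 gives 0.412 − 0.474 = −0.062, a spurious benefit. With equal exclusion and equal risk among those excluded, there is no bias under the null.

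**5. The same in counts (hypothetical).** Take 18/35 control and 13/35 RIPC events: 51.4% vs 37.1%, a 14.3-point difference. Exclude 4 controls and 1 RIPC patient, all with events: 14/31 vs 12/34, or 45.2% vs 35.3%, a 9.9-point difference. The loss is (14.3 − 9.9)/14.3 = 31%.

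**The case against.** The strongest reply is that the article never says these patients leave the non-MRI analyses. The only reason given for excluding unstable patients concerns the scan, so the entry may be a rule about MRI evaluability. Analysis sets are commonly left to a full protocol or SAP, the Ethics section claims CONSORT compliance, and the flowchart is not shown. This stands to the extent that removal from troponin T, MACE and cognition is the natural reading of a study-level exclusion, not an explicit statement. It does not remove the point: the criteria sit in the table of study exclusions beside the preoperative ones, and an SAP that kept everyone would contradict Table 1 and have to be reconciled with it.

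A second reply is that exclusions may be few. Patients are elective, those with ejection fraction below 30% are excluded, the Myocardial revascularization section calls escalation of support beyond dobutamine unlikely, and surgeons and intensive care physicians do not know the allocation. Blinding does limit exclusions driven by knowledge of arm. It does not stop a real effect of RIPC on instability.

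Third, a scan that cannot be done stays missing whatever it is called. That is true, and the count example in the working treats the excluded outcomes as known, which in practice they would not all be.

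Four stronger readings are tempting but unsupported:

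- *The result is biased, or a benefit is diluted.* No exclusion rates are given, and either direction is possible.
- *The highest-risk patients are removed.* That fits instability; a new MRI contraindication need not mark neurological risk.
- *MACE loses cases of cardiogenic shock.* Shock is not a MACE component in Outcome definitions, and nothing says that a death is classed as instability.
- *Five exclusions are exactly what the sample size allows.* The figure of 65 is back-calculated, not stated.

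**Conclusion.** The point holds as a risk of bias created by a rule that the protocol states. Two events that follow treatment are study exclusions, and for instability the article's own Background makes a link to both arm and outcome plausible. The comparison may be biased; size and direction cannot be determined. In the assumed scenarios the shift under no effect runs from zero to about 7 points (0.069 at 20% vs 10% with every excluded patient having the outcome), and a true −0.20 appears as anything from −0.222 to −0.149. These figures show only that in a trial of 70 a handful of exclusions can matter.

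The mismatch between rationale and rule does not depend on any assumed rate: inability to scan justifies missing MRI components and nothing more. How far the exclusion extends to the other endpoints rests on reading Table 1 as written.

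**What to change.** - In Table 1, delete the two entries as study exclusions and list them as reasons for a missing day-7 MRI. Drop the protocol-violation label for a new MRI contraindication, which is a postoperative event.
- State that all randomised patients are analysed in the assigned arm for troponin T and 3-month MACE, and for the neurocognitive tests wherever the patient can be tested.
- Report MRI non-completion by arm, with reasons.
- For the primary composite, include all randomised patients with a prespecified method for missing MRI components and a best/worst-case sensitivity analysis. The method must fit the rule by which the components are combined, which Outcome definitions does not give; this change does not choose one or add events to the composite.
- Keep the analysis of MRI completers as supportive.

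No assessment is added to the schedule, but already scheduled day-7 testing and 3-month follow-up must be completed for patients who would otherwise have been dropped. Recruitment is ongoing, so data on anyone already excluded should be recovered where possible.

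The statistical cost is that some primary outcomes will be partly missing or imputed. In the hypothetical count example, if the five outcomes were wholly unknown, the RIPC-minus-control difference would range from 12/35 − 18/35 = −17.1 points to 13/35 − 14/35 = −2.9 points. That width is honest uncertainty that a completers-only analysis would hide.

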### Ethics

The ethics committee of the University Hospital Center Zagreb evaluated and approved the conduct of this study (Registration No. 380-59-10106-13-195/292) in December 2013. Ethical standards in line with the Declaration of Helsinki involving research on human subjects will be strictly adhered to. This protocol complies with CONSORT guidelines [17].

### Sample size

The estimation of the approximate sample size for this study was based on an exact sign (binomial) test, assuming an effect size of 0.20. To account for potential postoperative contraindications for MRI and study consent withdrawals, an estimated 70 patients will be required to test the null hypothesis with an α value of 0.05 and a power of 0.90 [18].

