### Statistical analysis

The frequency distributions of primary and secondary study endpoints will be compared across the groups using 2 × 2 contingency tables. Continuous data will be presented as mean values ± standard deviation or medians with their respective interquartile range. Categorical variables will be presented as absolute numbers with percentages. Measures of association of categorical data will be derived from Fisher’s exact test. Analysis of continuous data will rely on the Mann-Whitney *U* test or Student’s *t* test. Comparisons of functional connectivity between regions of interest on pre- and postoperative rs-fMRI will be performed with the Wilcoxon matched-pairs test. Correlations between multiple variables of interest will be examined using Spearman’s or Pearson’s correlation coefficients. The choice between parametric and nonparametric statistical tools will be based on the normality of distribution. A two-tailed *P* value of less than 0.05 will be considered significant for all deployed statistical calculations. The data will be processed using the IBM SPSS Statistics software package (version 20.0; Somers, NY, USA).

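### The 70 patients and 90% power come from a one-sample sign test and do not apply to the planned two-arm Fisher comparison

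*Protocol article*

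**What the plan says.** Under Sample size, the protocol article bases N on a calculation "based on an exact sign (binomial) test, assuming an effect size of 0.20". It concludes that "an estimated 70 patients will be required to test the null hypothesis with an α value of 0.05 and a power of 0.90". The total is introduced by "To account for potential postoperative contraindications for MRI and study consent withdrawals", but no loss rate and no figure before losses is given.

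Under Allocation procedure and Intervention and control protocols, patients go either to preconditioning or to a control arm with an uninflated cuff. These are two separate groups, and nothing pairs patients across them.

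Under Statistical analysis, the frequency distributions of the primary and secondary endpoints "will be compared across the groups using" 2 × 2 contingency tables. "Measures of association of categorical data will be derived from" Fisher's exact test. Sidedness is explicit: "A two-tailed *P* value of less than 0.05 will be considered significant for all deployed statistical calculations". The only matched-pairs method named is the Wilcoxon test of connectivity before and after surgery, which works within patients and does not test one arm against the other.

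**The concern.** The test used to size the trial cannot perform the trial's primary comparison. A sign test asks whether one proportion, or one set of paired signs, departs from the known value 0.5. A two-arm comparison has to estimate both proportions, each from half the patients.

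The variance shows the difference. With 70 patients and a proportion near 0.5, the standard error of one proportion is √(0.25/70) = 0.060. The standard error of a difference between two arms of 35 is √(0.25/35 + 0.25/35) = 0.120, twice as large. A shift of 0.20 is then 3.3 standard errors in the first setting and 1.7 in the second.

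At stake is how a non-significant primary result may be read. Next to a stated power of 90%, it looks like good evidence against an effect of the assumed size. If the power for the planned test is far lower, it is not.

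**Working it through.** **Inputs from the protocol article.** Exact sign (binomial) test, effect size 0.20, N = 70 in total, alpha 0.05, power 0.90 (Sample size); two-tailed 0.05, 2 × 2 tables, Fisher's exact test (Statistical analysis).

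**Inputs not in the article, taken as assumptions.** 1:1 allocation, so 35 per arm; 0.20 read as an absolute difference between arms; control event rate varied over its whole range; all 70 evaluable, then 32 per arm as a sensitivity case.

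**Step 1: reproduce the plan's figure.** For a sign test, an effect size of 0.20 means p = 0.50 + 0.20 = 0.70 against 0.50. Let r be the smallest count with P(X ≥ r | N, 0.5) ≤ 0.025. Power is P(X ≥ r | N, 0.7) + P(X ≤ N − r | N, 0.7).

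| N | r | actual two-sided alpha | power |
|---|---|---|---|
| 63 | 40 | 0.043 | 0.895 |
| 65 | 41 | 0.046 | 0.910 |
| 66 | 42 | 0.036 | 0.895 |
| 69 | 44 | 0.029 | 0.895 |
| 70 | 44 | 0.041 | 0.922 |

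The smallest N with at least 90% power is 65. Because exact power is saw-toothed, it stays at or above 90% for every N only from 70 upward. A one-sided calculation would need 53 (power 0.914). The stated 70 is thus consistent with a one-sample calculation.

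**Step 2: power of the planned test.** With control rate p₁, preconditioning rate p₂ = p₁ − 0.20 and n per arm, power is the sum of Bin(i; n, p₁) × Bin(j; n, p₂) over all tables (i, j) whose two-sided Fisher P value is at most 0.05.

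| control vs preconditioning | 35 per arm | 32 per arm |
|---|---|---|
| 20% vs 0% | 0.728 | 0.640 |
| 25% vs 5% | 0.550 | 0.484 |
| 30% vs 10% | 0.455 | 0.411 |
| 40% vs 20% | 0.357 | 0.329 |
| 50% vs 30% | 0.312 | 0.298 |
| 60% vs 40% | 0.280 | 0.298 |
| 70% vs 50% | 0.312 | 0.298 |
| 80% vs 60% | 0.357 | 0.329 |
| 90% vs 70% | 0.455 | 0.411 |
| 95% vs 75% | 0.550 | 0.484 |
| 100% vs 80% | 0.728 | 0.640 |

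For control rates of 30–90% the range is 0.28–0.46 at 35 per arm and 0.30–0.41 at 32 per arm. The slightly higher minimum at 32 comes from the discreteness of Fisher's test. The maximum at any control rate is 0.728.

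**Step 3: difference detectable with 90% power at 35 per arm.** I searched downward from each control rate in half-point steps for the smallest reduction with Fisher power of at least 0.90. From control rates of 30, 40, 50, 60, 70, 80 and 90% it is 28.5, 33.5, 37.5, 39.5, 41.5, 39.5 and 36 points.

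**Step 4: size needed for a 20-point difference.** n per arm = [1.960 √(2p̄(1 − p̄)) + 1.282 √(p₁(1 − p₁) + p₂(1 − p₂))]² / 0.20². For 50% vs 30%, (1.358 + 0.869)² / 0.04 = 124 per arm. Over control rates of 30–90% this gives 82–130 per arm, or 92–140 with continuity correction.

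**The case against.** A reader might infer that the trial's true power simply is 28–46%. The document does not support that as a fact. It says "assuming an effect size of 0.20" without a scale. In the sign test the figure is a distance from 0.5; treating it as a between-arm risk difference is a second and different reading. The range also needs 1:1 allocation, no losses and a control rate of 30–90%, none of which is stated. High control rates are not remote if any one of the three components counts as an event, though Outcome definitions does not give that rule. At 95% vs 75% power is 55%, and at 100% vs 80% it is 73%. This objection stands, so the figures must be given as conditional. It does not rescue the 90%, which is reached at no control rate under this reading.

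A reader might also subtract 65 from 70 and infer a loss allowance of 5 patients, about 7%. That cannot be derived. If the starting figure was 65 the allowance is 5, if it was 70 it is 0, and if the calculation was one-sided (53) it is 17.

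Nor is this a slip of arithmetic: the stated N is consistent with the stated test. The fault is the choice of test. As a condensed article, the text may also fairly leave the control event rate to a fuller document, so that gap is not a fault in itself. A fuller document could not, however, make a sign-test power apply to a two-arm Fisher comparison.

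Finally, 70 might have meant patients per arm. The text gives it as the number of patients required and does not say per arm. Even then, Fisher power for a 20-point difference would be 0.60–0.81 at control rates of 30–90%.

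**Conclusion.** The point holds as a mismatch between test and design. The 90% power belongs to a one-sample test against 0.5 and does not apply to the comparison of two independent arms that the analysis section plans. This conclusion rests on the document alone.

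Its size is conditional. With 0.20 as a 20-point absolute difference, 1:1 allocation and all 70 evaluable, Fisher power is about 28–46% for control rates of 30–90% and below 75% at any control rate. With 32 evaluable per arm it is about 30–41% over the same control rates. Under these assumptions the trial would, for control rates of 30–90%, miss a 20-point effect more often than detect it. How large the allowance for losses was cannot be determined.

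**What to change.** Replace the sign-test statement under Sample size with a calculation for two independent proportions, using Fisher's exact test at two-sided 0.05. It should state the scale of the effect, the assumed control event rate, the allocation ratio and the expected attrition.

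Keep N = 70 and restate what it delivers: either the actual power for the assumed difference, or the difference detectable with 90% power. At 35 per arm the latter is about 29–42 points, depending on the control rate. Add that the primary result will be reported as a risk difference with its 95% CI, so that a non-significant result is not read as excluding a 20-point effect.

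The change is one of wording and needs no extra patients. Its cost is that the stated power becomes much less favourable.
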